### Study design

Effect of EARLY administration of DEXamethasone in patients with COVID-19 pneumonia without acute hypoxemic respiratory failure and risk of development of acute respiratory distress syndrome (EARLY-DEX COVID-19) study is a multicenter, randomized, controlled, open-label, parallel-group trial involving 252 hospitalized patients with COVID-19 pneumonia who do not require supplemental oxygen on admission, and laboratory biomarkers related to severe COVID-19 disease are detected. Patients will be randomized and enrolled in Spain. Study sites are listed in the Appendix.

The trial was designed in accordance with the Declaration of Helsinki [22], the Convention of the European Council related to human rights and biomedicine, and within the requirements established by Spanish legislation in the field of biomedical research, the protection of personal data, and bioethics, which was registered on 8 April 2021 at http://www.clinicaltrials.gov with identification no. NCT04836780. The study protocol (version 1.2, 17 April 2021) was approved by the Ethics Committee for investigation with medicinal products of the Comunidad de Madrid, Spain, and the institutional review boards of all participating hospitals (Additional file 1). The trial was approved by the Spanish Agency of Drugs and Medical Devices as a clinical randomized study with drugs on 25 May 2021 (Additional file 2 in Spanish).

Prior to any activity carried out as part of the research, subjects will receive a concise and focused presentation of key information about the clinical trial, verbally and with a written consent form. To be included, written informed consent will be requested from patients’ relatives or legal representative by the local investigators. Following the recommendations of the Spanish Agency of Medicines and Medical Devices, during the COVID-19 pandemic, patient consent can be obtained orally and preferably before an impartial witness, documenting it in the patient’s medical records [23]. The forms have been reviewed by the Ethics Committee that authorized the trial.

Our protocol followed the SPIRIT (Standard Protocol Items: Recommendations for Interventional Trials) guidelines [24]. See Additional file 3 for the SPIRIT checklist of the study protocol.

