### Randomization

Eligible, consenting patients will be randomly assigned in a 1:1 ratio to receive either dexamethasone plus standard of care (intervention group) or standard of care alone (control group). Randomization will be done within the REDCap system with unpredictability of assignments. Our statistician created a randomization schedule using a permuted block design, so equal numbers are assigned to each group. This system ensures a balanced allocation of subjects to the study arms. Records of individual assignments to each group will be de-identified (user number and centre ID instead of patients’ names), sequentially numbered, and stored on a secure computer system. Local investigators in participating centres are the only authorized personnel to interact with the radomization system through a username and password. Once eligibility is confirmed in the electronic case report form, the treatment group is assigned by the system. Dexamethasone will be provided free of charge for this study by the organization funding. According to the ethical principles for medical research of the Declaration of Helsinki, the use of no placebo (no intervention) is acceptable when no proven intervention exists. The Spanish Agency of Drugs and Medical Devices and the Ethics Committees did not mandate a blinded design or the administration of a placebo.

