### Intervention

Patients in the intervention group will receive an intravenous dose of 6 mg once daily from day 1 to day 3, followed by an oral dose of 6 mg once daily from day 4 to day 7 (Fig. 1). For participants unable to take an oral drug, intravenous dexamethasone will be given. We selected the same dose as the RECOVERY trial. Participants randomized to the control group will receive a standard of care. Given that pulmonary disease can progress rapidly in patients with COVID-19, patients will be closely monitored. For improving intervention adherence, a real-time medication monitoring system will offer monitoring of participants’ medication control combined with a short message service (SMS) after discharge. Study participants will receive the best standard of care according to the current COVID-19 Treatment Guidelines. Hospitalized patients who do not require supplemental oxygen can receive anticoagulants for the prevention of venous thromboembolic disease, gastric ulcer prophylaxis, hydration, antipyretics, antibiotics, and bronchodilators. Corticosteroids in patients requiring oxygen support in the control group will be received. In addition, remdesivir, tocilizumab, baricitinib, tofacitinib, and sarilumab will be considered in case of a worsening of disease status [13]. All chronic medication prescribed to the patient is permitted to continue at the discretion of the responsible physician/investigator.

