### Secondary outcomes

Secondary outcomes are:Requirement of non-invasive ventilation or invasive mechanical ventilationHospital length of stayAll-cause mortality during the 90-day period following enrolmentAll-cause readmission during the 90-day period following discharge

Local investigators will contact the patient or relatives by phone to ensure the status of the patient on day 90 after randomization. The lead investigator in each site will confirm the recorded 90-day readmission.

The incidence of adverse events and serious adverse events during the study period will be reported.

Results will be communicated at scientific meetings and submitted for publication in peer-reviewed international journals, regardless of the outcome.

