### Sample size

We powered the study to assess whether the intervention would reduce the incidence of ARDS. Based on available evidence, we estimate a 30% risk of ARDS in the control group [2]. We are looking for an ARDS 10% absolute reduction in the intervention group. Assuming 80% power and two-sided alpha = 0.05, 226 participants would be needed to detect the resulting reduction of ARDS from 30% in the control group to 20% in the intervention group. We adopted a sample size of 252 (126 per group) to compensate for the potential loss to follow-up of some participants.

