### Safety assessment

All patients who have been randomized and have taken at least one dose of treatment will be analysed for safety. Safety outcomes include bleeding, metabolic complications (ketoacidosis, hyperglycaemic hyperosmolar state, hyperglycaemia requiring new use of insulin), hypertension, new cardiac arrhythmia, allergic reaction, psychiatric disorders, new infections, and chorioretinopathy or blurred vision. All adverse events occurring after entry into the study and until hospital discharge will be recorded in the patient’s health record. An adverse event that meets the criteria for a serious adverse event between study enrolment and hospital discharge will be reported to the local Institutional Review Board. A serious adverse event for this study is any untoward medical occurrence that is believed by the investigators to be causally related to the study-drug and results in any of the following: life-threatening condition, severe or permanent disability, prolonged hospitalization, or a significant hazard as determined by the Data Safety Monitoring Board. Serious adverse events occurring after a participant is discontinued from the study will not be reported unless the investigators feel that the event may have been caused by the study drug.

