Patients receiving glucocorticoids should be monitored for adverse effects. These include hyperglycaemia, an increased risk of infections (including bacterial, fungal, and *Strongyloides* infections) and prolonged viremia. However, in RECOVERY trial record, only four serious adverse events (0.19%) were deemed by the investigators to be related to dexamethasone (two of hyperglycaemia, one of gastrointestinal haemorrhage, and one of psychosis) [15]. Evidence is inconsistent on the viral clearance delay of glucocorticoid-treated COVID-19 patients [32, 33]. Nevertheless, it seems that a high or medium dose, but not a low dose of glucocorticoids, leads to viral clearance delay which seems clear [33]. The rates of infections in patients with COVID-19 receiving glucocorticoids are uncertain. In the same way as viral clearance, prolonged high-dose glucocorticoids increase the risk of the appearance of severe microbial infections [34]. At the proposed dose and period of treatment of dexamethasone in this study, low toxicity and good tolerability profiles are expected.

The major limitation of our study is that it is not blinded and lacks the use of a placebo. However, the primary endpoint of the trial is clear, causing the influence of placebo treatment to be smaller. In addition, with placebo treatment, the trial design would be more complex and the cost more expensive. Second, our study design will not allow us to conclude whether the administration of dexamethasone at different doses and for longer or shorter periods would have improved outcomes. Nevertheless, if our hypothesis is correct, our findings will provide novel insights about the management of patients with COVID-19 pneumonia without additional oxygen requirements and at risk of progressing to severe disease.

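### Investigator attribution to the study drug is part of the serious adverse event definition, so control patients can have none and SAE incidence cannot be compared between arms

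*Protocol article*

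**What the plan says.** All places below are in the protocol article.

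- **Definition (Safety assessment).** An SAE is "any untoward medical occurrence that is believed by the investigators to be causally related to the study-drug and results in any of the following". Four outcomes are then listed: a threat to life, serious or lasting disability, a longer hospital stay, and a hazard that the monitoring board judges significant. Attribution and outcome are joined by *and*, so both are required. Death is not named.
- **Use of the definition.** Events that meet it between enrolment and discharge go to the local Institutional Review Board (Safety assessment). Under Secondary outcomes: "The incidence of adverse events and serious adverse events during the study period will be reported". Statistical analysis names no SAE-specific test, but compares qualitative variables in general by chi-squared or Fisher's exact test.
- **Design.** Study design describes a "multicenter, randomized, controlled, open-label, parallel-group trial involving 252 hospitalized patients". Under Randomization, the control group is assigned standard of care alone, with no placebo. Sample size gives 126 per group.
- **Corticosteroids in controls (Intervention).** "Corticosteroids in patients requiring oxygen support in the control group will be received".
- **After discontinuation (last sentence of Safety assessment).** SAEs arising after a participant has been discontinued are left unreported, except where the investigators suspect the drug.
- **Safety population (Safety assessment).** Patients must be randomized and have had at least one dose of treatment.

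**The concern.** Seriousness and causality are separate properties of an event. Seriousness can be judged alike in both arms. Causality under open-label treatment cannot, and for a patient who was assigned no study drug the question has no meaning. Once causality is part of the definition, the SAE table no longer compares like with like.

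What is at stake is the interpretation of non-fatal serious harm. The Discussion names infection as a glucocorticoid risk and calls infection rates in treated COVID-19 patients uncertain. It also recalls that RECOVERY showed no benefit in patients without respiratory support. A serious infection on dexamethasone that the investigator puts down to COVID-19 would not be classed as an SAE and would not reach the Institutional Review Board as one. The same infection in a control patient could not be classed as one at all.

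**Working it through.** The article states no SAE rate and no SAE power, so there is no figure to reproduce. The check is first of the logic, then of how far the count can mislead.

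**1. Logic.** Let p_D and p_C be the true all-cause SAE rates on dexamethasone and control, and q the share of dexamethasone events that investigators attribute to the drug. Under the written definition:

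- expected control count = 126 × p_C × 0 = 0, whatever p_C is;
- expected dexamethasone count = 126 × p_D × q.

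The true control rate p_C does not affect the result.

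**2. Internal consistency.** The last sentence of the section makes suspected causation an exception that brings later SAEs back into reporting. An exception of that kind has work to do only if some SAEs are not drug-related. The definition has already excluded those.

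**3. Smallest count that looks significant.** With equal arms and zero control events, the two-sided Fisher p-value for k events is 2 × C(126, k) / C(252, k).

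- k = 5: p = 0.060
- k = 6: p = 0.029

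Six attributed events are enough at the 0.05 level.

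**4. Chance of reaching six.** This is P(X ≥ 6) with X ~ Binomial(126, p_D × q). The rates and shares are assumptions, because the article gives neither.

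| True SAE rate on dexamethasone | q = 0 | 10% | 25% | 50% | 100% |
|---|---|---|---|---|---|
| 5% | 0% | 0.0% | 0.5% | 9.7% | 60.6% |
| 10% | 0% | 0.2% | 9.7% | 60.6% | 98.9% |
| 20% | 0% | 4.2% | 60.6% | 98.9% | about 100% |

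The table can be read in three ways.

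- *Spurious excess.* If both arms truly have 10%, every figure in that row is a false signal, from 0% to 98.9%.
- *Hidden excess.* If dexamethasone truly has 20% and control less, but only 10% of events are attributed, the expected count is 126 × 0.20 × 0.10 = 2.5, and the chance of a significant result is 4.2%. It would be the same 4.2% if control also had 20%.
- *Missed benefit.* If dexamethasone has 5% and control 20%, with half attributed, the expected counts are 126 × 0.05 × 0.50 = 3.15 against 0. The table would point the wrong way.

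**5. After correction.** If SAEs are counted in both arms regardless of cause, equal true rates of 5%, 10% and 20% give 6.3, 12.6 and 25.2 expected events per arm. The exact type I error of the same Fisher test is then 2.17%, 2.94% and 3.45%, below the nominal 5% in each case.

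**The case against.** The strongest reply is that little safety information is lost.

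- All-cause death is in the 30-day primary composite and is a 90-day secondary outcome, in both arms and without attribution.
- New infections, bleeding, metabolic complications, arrhythmia and psychiatric disorders are named safety outcomes with no causality condition. Common dexamethasone effects, including new infection, are asked about daily.
- All adverse events to discharge are recorded whatever their cause.
- Under Data management, the Data and Safety Monitoring Board has access to the trial dataset, so it is not confined to attributed SAEs.

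All of this stands, and it sets the limits of the point. A reader might infer that excess deaths or infections on dexamethasone would never be counted. The document does not support that: they would be counted, but not as SAEs. What remains is that recording an adverse event does not grade its seriousness by arm, and mortality does not cover non-fatal serious harm.

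A second reply is that no SAE test is specified, so no comparison can be void. That is fair as to wording. A list of attributed SAEs is usable if labelled as drug-related. The article instead promises SAE incidence without that label, and its general rule for qualitative variables would apply a between-arm test.

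A third reply is that controls who need oxygen receive corticosteroids, to which an investigator might attribute an event. That treatment is background care and not the assigned study drug, so the plain reading still gives zero. If some sites read it otherwise, the count would also vary by site.

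A reader might also infer that the table will show 0 against 0 whatever the truth. The Discussion reports that in RECOVERY "only four serious adverse events (0.19%) were deemed by the investigators to be related to dexamethasone". At 0.19%, 126 patients give 126 × 0.0019 = 0.24 expected events and a (1 − 0.0019)^126 = 0.787 chance of none. That rate comes from another trial, which included ventilated and oxygen-treated patients and treated for up to 10 days against 7 here. It shows one possible outcome. The table above shows that the opposite distortion is equally possible.

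**Conclusion.** The point holds in a limited form. On the plain text the control SAE count is zero by construction and the dexamethasone count reflects unblinded attribution, so SAE incidence by arm is not interpretable as a randomized comparison. The direction and size of the distortion cannot be fixed from the document. At an assumed equal rate of 10%, the chance of a spurious significant excess ranges from 0% to 98.9%, and the same mechanism can hide a true excess or a benefit. These figures rest on assumed event rates and attribution shares, and on applying the article's general test to SAEs. The zero in the control arm rests only on the definition and on who is assigned the study drug.

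The primary outcome, mortality, the named safety outcomes and the overall adverse event record are not affected. Omitting death from the SAE list loses no mortality data, but it leaves the SAE table incomplete. The damage is to SAE classification, tabulation and reporting to the Institutional Review Board, and to the consistency of the section with its own last sentence.

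**What to change.** 1. Define an SAE by outcome alone, identically in both arms, and add death to the listed outcomes.
2. Record investigator-assessed causality as a separate field.
3. Tabulate all-cause SAEs by arm, and show drug-related SAEs as a labelled subset.
4. Reword the sentence on events after discontinuation so that it fits the new definition.
5. Word the safety population so that control patients are clearly included. Read literally, the requirement for at least one dose of treatment may leave them out.

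The cost is a change to protocol and eCRF wording and somewhat more SAE forms. The article reports recruitment since June 2021, so patients already enrolled would need their recorded adverse events classified again under the new definition. The health record should allow this up to discharge, where recording of adverse events ends.

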**Fig. 1 Fig1:**
[figure not shown]
Study design diagram

For a trial participant, the assigned study intervention will be modified or discontinued by trial investigators if serious adverse events occur during the study period or withdrawal of participant consent. Regardless of any decision to modify or discontinue their assigned intervention, study participants will be retained in the trial whenever possible to enable follow-up data collection and prevent missing data.

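### Serious adverse events are filtered by unblinded attribution to the study drug, in the definition and again after a participant leaves the study, so their incidence cannot be compared between arms

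*Protocol article*

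**What the plan says.** The relevant statements in the protocol article are these.

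- **Safety assessment, definition.** To count as a serious adverse event, an occurrence must be "believed by the investigators to be causally related to the study-drug and results in any of the following" (a list of seriousness criteria follows).
- **Safety assessment, window and recipient.** Serious events "between study enrolment and hospital discharge will be reported to the local Institutional Review Board".
- **Safety assessment, after leaving the study.** "Serious adverse events occurring after a participant is discontinued from the study will not be reported unless the investigators feel". The exception is for events in which dexamethasone is suspected as a cause.
- **Safety assessment, adverse events in general.** "All adverse events occurring after entry into the study and until hospital discharge will be recorded in the patient’s health record". No arm or causality condition is attached.
- **Secondary outcomes.** "The incidence of adverse events and serious adverse events during the study period will be reported". Again there is no causality condition.
- **Intervention (text after Fig. 1).** "the assigned study intervention will be modified or discontinued by trial investigators if serious adverse events occur during the study period", or if consent is withdrawn. Whatever is decided about the intervention, "study participants will be retained in the trial whenever possible to enable follow-up data collection".

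Under Randomization, the control arm is assigned standard of care alone. The Discussion acknowledges that the trial is unblinded and has no placebo.

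**The concern.** A randomised comparison of serious events needs the same counting rule in both arms. Here the rule depends on whether the investigator, who knows the allocation, links the event to the study drug. In the dexamethasone arm the count therefore depends on opinion. In the control arm there is no assigned study drug to blame.

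The resulting counts could mislead in either direction. With equal true risks, dexamethasone would show an excess by construction. With sparing attribution, a real excess could be reduced to a handful of events and look reassuring. The Discussion describes infection rates under glucocorticoids in COVID-19 as uncertain. That is the kind of question a comparison by arm can answer and case-by-case attribution cannot.

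**Working it through.** The plan states no serious-event rate, attribution rate or discontinuation rate, so it has no figure to reproduce. The check is mainly one of wording.

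**1. The definition.** Causation by the study drug is part of what makes an event serious. An event not attributed to the drug is therefore not a serious adverse event at any time from enrolment onward, in either arm. A control participant has no assigned study drug, so the condition can hardly be met.

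**2. The sentence on later events.** It applies to a participant discontinued *from the study*. The Intervention section deals with a different event, stopping or modifying the *assigned intervention*, and keeps those participants in the trial where possible. The sentence therefore covers only those who leave the study.

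**3. The two together.** Under the present definition every serious event is already believed to be drug-related, so the exception in the later sentence covers essentially all of them and the sentence removes almost nothing further. If only the definition were corrected, the later sentence would bring the attribution filter back. If only the later sentence were corrected, the definition would leave the filter in force for everyone.

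**4. The window.** Safety assessment ends routine recording and reporting at hospital discharge. Secondary outcomes promises incidence over the study period, and the section on data collection sets follow-up at 90 days. The end of counting is therefore not settled.

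**5. Illustration of the definition.** Reported events = N × r × a.

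- N = 126 per arm (Sample size).
- r = true serious-event risk, equal in both arms, assumed 5–20%.
- a = share attributed to the study drug, assumed 10–100% under dexamethasone and taken as 0 in control.

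| | Low | High |
|---|---|---|
| True events per arm, N × r | 126 × 0.05 = 6.3 | 126 × 0.20 = 25.2 |
| Reported, dexamethasone | 6.3 × 0.10 = 0.63 | 25.2 × 1.00 = 25.2 |
| Reported, control | 0 | 0 |

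A true difference of zero would appear as a difference of 0.6 to 25.2 events.

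**6. Illustration of the later sentence alone, with the definition already corrected.** Let d be the share who leave the study, assumed 5–20%, and let 5–20% of those have a later serious event. True later events per arm are 126 × 0.05 × 0.05 = 0.3 to 126 × 0.20 × 0.20 = 5.0. Dexamethasone would report 0.03 (0.315 × 0.10) to 5.0 of them and control none. These ranges are assumptions, not estimates. They show only that this sentence reaches fewer people than the definition.

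**The case against.** The strongest reply is that the filter matters less than it seems. All adverse events are recorded until discharge in both arms. The listed safety outcomes, such as bleeding and new infections, carry no attribution condition. Death from any cause and readmission are collected to day 90 in both arms. The reporting rule for in-hospital serious events is addressed to the local review board, where a relatedness test has a purpose. Ending active collection when someone leaves a study, with an exception for suspected drug effects, is also a defensible choice.

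Much of this stands. It rules out several stronger readings that a reader might infer:

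- **That participants taken off dexamethasone for a serious event lose their later events.** The text does not say so. They are to be retained, and the later sentence concerns leaving the study.
- **That serious harm in controls can never come to light.** Deaths, readmissions and in-hospital adverse events are captured. Controls who come to need oxygen receive corticosteroids, which leaves some ambiguity about what counts as the study drug.
- **That the sentence on later events is the main fault.** The definition in the same section is the larger source.
- **That the loss allowance of 252 − 226 = 26 participants sizes the problem.** It is an allowance for loss to follow-up. Events in people who cannot be reached are largely unobserved under any reporting rule.

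The reply does not rescue the serious-event incidence itself. That output is promised without a causality condition, while the only definition given contains one. A non-fatal serious event after discharge that does not lead to readmission has no other stated route into the data.

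**Conclusion.** The point holds for the serious-event comparison, not for safety data as a whole. As written, reported serious-event counts would not be comparable by arm, because they depend on unblinded attribution to a drug that only one arm is assigned. The causality condition in the definition is the main cause, and the sentence on events after leaving the study is a smaller, second one.

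The size of either cannot be estimated from the documents. The figures above rest on assumed risks, attribution shares and departure rates, on equal true risk in both arms, and on no control event being attributed to the study drug. The conclusion about comparability needs only the last of these, and only approximately. The change should be made, with both sentences treated as one amendment.

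**What to change.** Amend the Safety assessment section as follows.

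1. Define a serious adverse event by its seriousness criteria alone, and remove the causality condition.
2. Replace the sentence on later events with a rule that serious adverse events are reported in both arms, whatever the suspected cause and whether or not the intervention was stopped, for as long as the participant remains in follow-up and consents to data collection.
3. Record the investigator's judgement of relatedness as a separate field, so that it can be tabulated without deciding what is counted.
4. Reconcile the discharge cut-off with the incidence over the study period promised under Secondary outcomes. State one window for both arms, and use the day-30 and day-90 contacts already planned to collect events after discharge.

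The cost is a safety-section amendment, a few more event forms and slightly longer follow-up calls. Nothing more can be collected from participants who withdraw consent to data collection, and the amended text should say so.
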